**PROMs**			
HRQoL	EQ-5D-5L questionnaire, assesses five dimensions of health: mobility (1), self-care (2), usual activities (3), pain/discomfort (4), and anxiety/depression (5) [31, 32]. Each dimension is rated on a 5-level scale, ranging from no problems (1) to extreme problems (5). Additionally, the EQ-5D-5L includes include a 0–100 VAS.	Survey	Baseline, at 6 and 12 months
**Symptom burden**	Four subdomains of the EORTC QLQ-H&N-35 questionnaire (weight loss, speech, swallowing function and pain) [30]. The H&N35 employs a 4-point response scale (‘not at all’ to ‘very much’), with higher scores indicating a higher symptom burden.	Survey	Baseline, at 6 and 12 months
**Fear of recurrence**	CWS, 6 items on worries after cancer treatment rated on a 4-point scale from almost never/ not at all to almost always/ very much [34].	Survey	Baseline, at 6 and 12 months
**Other**			
Visit frequency	Amount of visits (scheduled and extra visits)	Electronic patient file	End of follow up period
**Travel distance**	Total distance travelled (kilometres) from the patient’s home address to the hospital by car	As indicated by Google Maps	End of follow up period
**Travel time**	Subjectively reported travel time, for the patients and their care givers	Survey	Baseline and at 6 months
**CO_2_ emission**	Estimation of CO_2_ emission caused by travel to the hospital for follow-up	Calculated from the travel distance (kilometres) and the mean emission per kilometre [36]	End of follow up period

Abbreviations: PREMs: patient-reported experience measures; NRS: numeric rating scale; CQI: consumer quality index; PROMs: patient-reported outcome-measures; HRQoL: health-related quality-of-life; VAS: visual analogue scale; CWS: cancer worry scale; EORTC QLQ-H&N-35: European Organisation for Research and Treatment of Cancer Quality of Life Questionnaire Head and Neck Module 35; CO_2_: carbon-dioxide.

### Sample size and recruitment

A power analysis was performed to calculate the sample size needed to answer our primary research question. As telemedicine follow-up has not been studied in HNC patients, power analysis was based on data from non-oncologic populations [26–28]. Most of these studies are one-armed studies. These studies reported a mean patient satisfaction, measured with a NRS or VAS, of 8.6 to 8.8, with one study noting a baseline score of 8.2. Although these results may not be representative of the HNC population, we based our expectations with regard to the primary outcome on these studies, nonetheless. Patient satisfaction is estimated at 9 (standard deviation [SD] 1.8) in the intervention arm and 8 (SD 1.8) in the control arm. To detect a clinically relevant difference of 1 point with 80% power and a two-sided alpha of 0.05, at least 41 patients per group are required. With an expected drop-out of 10%, a total of 90 patients will be included. This analysis was performed using G*Power (version 3, Heinrich-Heine-Universität Düsseldorf, Germany). Patients are first informed about the study by their treating head and neck oncologist in the HNOC. If a patient meets the eligibility criteria, the researcher will provide additional information, and an informed consent will be obtained.

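### The stated 41 patients per group does not follow from the stated two-sided inputs: 52 are needed, and 41 gives about 70% power, not 80%

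*Protocol article*

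**What the plan says.** The section Sample size and recruitment gives every input. On the primary outcome, "Patient satisfaction is estimated at 9 (standard deviation [SD] 1.8) in the intervention arm and 8 (SD 1.8) in the control arm". The target is worded "To detect a clinically relevant difference of 1 point", and the result follows directly: "with 80% power and a two-sided alpha of 0.05, at least 41 patients per group are required". The total is then set: "With an expected drop-out of 10%, a total of 90 patients will be included". The calculation is attributed to G*Power version 3, with no mention of the test family or the tails setting.

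Elsewhere, Allocation to study groups gives a 1:1 ratio. Statistical analysis names the independent t-test for normally distributed outcomes and the Mann-Whitney test otherwise, and lists no covariate-adjusted comparison. Outcomes makes the 0–10 satisfaction score at 12 months the primary outcome.

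**The concern.** A 1-point difference with SD 1.8 is a standardised difference of about 0.56. Two-sided testing at 0.05 with 80% power usually needs a little over 50 per group for an effect of that size, so 41 looks too small. The gap of 10 to 11 patients per group is too large to be rounding or a choice between formulas.

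At stake is the power of the sole primary comparison. If the declared 80% is wrong, a non-significant result will be read as coming from an adequately powered trial when the real risk of missing the target difference is half as large again as stated.

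**Working it through.** **Inputs** (Sample size and recruitment; allocation ratio from Allocation to study groups): difference δ = 9 − 8 = 1; SD σ = 1.8 in each arm; two-sided α = 0.05; power 80%; 1:1 allocation; 10% drop-out; total 90. The standardised difference is d = 1/1.8 = 0.556.

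**Step 1. Reproduce the stated figure, two-sided as declared.** Normal approximation:

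n per group = 2 (z₁₋α/₂ + z₁₋β)² σ²/δ² = 2 × (1.960 + 0.842)² × 3.24 = 50.9, so 51.

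The exact noncentral t calculation gives 51.8, so 52. Power is 79.3% at 51 and 80.1% at 52. The stated 41 is not reproduced.

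**Step 2. Look for a setting that does give 41.** With one-sided α = 0.05:

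n per group = 2 × (1.645 + 0.842)² × 3.24 = 40.1, so 41.

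The noncentral t gives 40.76, so 41. One-sided power is 79.3% at 40 and 80.2% at 41. The match is exact by both methods.

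**Step 3. Try the Mann-Whitney test.** Dividing the two-sided t-test size by the asymptotic relative efficiency gives 55 (normal parent), 60 (minimum efficiency), 48 (logistic) or 35 (Laplace) per group. None is 41.

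**Step 4. Two-sided power of the planned trial** (noncentral t, d = 0.556):

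| Evaluable per group | How it arises | Power |
|---|---|---|
| 40.5 | 90 × 0.9 = 81 in total | 69.5% |
| 41 | stated requirement | 70.0% |
| 45 | all 90, no drop-out | 74.1% |
| 52 | needed for 80% | 80.1% |

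Under Mann-Whitney with a normal parent, power at 41 per group is about 68%.

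**Step 5. Detectable difference.** At 41 per group, two-sided 0.05 and 80% power, the detectable difference is 1.127, or about 1.13 points.

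**Step 6. Size needed for the declared power.** 52/(1 − 0.10) = 57.8, so 58 per group and 116 randomised, against the planned 90.

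**Step 7. Drop-out step (minor).** The plan's own requirement is 2 × 41 = 82 evaluable patients. 82/0.9 = 91.1, so 92 in equal arms. With 90 randomised, 81 remain, one short.

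**Step 8. What adjustment for baseline could recover.** Adjusting for a baseline score with correlation r to the 12-month score reduces the residual SD to 1.8 × √(1 − r²). The article gives no r, so a range is shown:

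| Assumed r | Power at 41 per group | Power at 40.5 per group |
|---|---|---|
| 0.2 | 71.8% | 71.2% |
| 0.3 | 74.1% | 73.5% |
| 0.4 | 77.4% | 76.9% |
| 0.46 | 79.9% | 79.4% |
| 0.5 | 81.8% | 81.4% |

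Reaching 80% needs r of about 0.46 with 41 per group, or just over 0.47 with 81 completers.

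**The case against.** The strongest objection is about cause. The article does not give the tails setting, so a one-tailed run is inferred from the exact match. A mis-stated SD is another possibility: two-sided testing with SD 1.59 gives 40.7, so 41, with 80.3% power. If the SD actually used was about 1.6, the 80% would be right and the 1.8 wrong. This stands as a limit on what can be said about the origin of the error, but it does not rescue the paragraph. The article gives 1.8 for both arms, and under either explanation the stated size contradicts the stated inputs.

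The drop-out gap is small. 82 × 1.1 = 90.2, so 90 follows a common add-10% convention, and the gap costs one patient and half a percentage point of power. That is fair, and the conclusion does not rest on it.

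The low power for smaller effects is a separate question. The cited means of 8.6 to 8.8, set against the single cited baseline of 8.2, suggest gaps of 0.4 to 0.6 points, where power at 41 per group is 17% to 32%. But the article sizes the trial on a difference it calls clinically relevant, which is legitimate, and it says openly that its sources may not be representative. These figures show only that the assumed effect leaves no cushion.

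Finally, the shortfall neither biases the estimate nor inflates the type I error, and the planned 95% confidence intervals will show the imprecision. That limits the harm, but the power claim is still incorrect.

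**Conclusion.** The concern holds. With the article's own inputs, a two-sided test at 0.05 needs 52 per group; 41 per group gives 70.0% power and the expected 81 completers give 69.5%. Even with no drop-out at all, 90 patients give 74.1%. The type II error for a 1-point difference is about 30% instead of 20%.

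This rests on SD 1.8 being the intended value, on an unadjusted comparison, and on the t-test. Mann-Whitney power depends on the shape of the distribution. Nothing in the article mentions a one-sided test, a different SD or an adjusted analysis that would justify 41.

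**What to change.** First check the saved G*Power settings, to confirm whether one tail was selected or a different SD was entered. If SD 1.8 is confirmed, keep the two-sided test and correct the sample size paragraph, for example: 41 evaluable patients per group give 70% power at two-sided alpha 0.05 for a 1-point difference with SD 1.8, or 80% power for a difference of 1.13 points; 90 randomised with 10% drop-out leave 81 evaluable. This costs a wording change and a less favourable power figure, and no patients.

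To recover power at 90 patients, prespecify a primary analysis adjusted for baseline satisfaction, which is already collected before randomisation, and report the adjusted power over a range of correlations as in the working. The 80% should be claimed only as conditional on a correlation of about 0.46 to 0.47 or more. That is not assured, because intervention patients may be rating a different hospital at 12 months from the one they rated at baseline.

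If 80% power for 1 point is to be kept with the unadjusted test, the trial needs 116 randomised patients, 26 more than planned.

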### Allocation to study groups

An independent researcher will generate the randomisation chart to ensure allocation concealment for the patient, clinician and researcher. Randomisation will be performed in REDCap with a 1:1 allocation ratio. Block randomisation and stratification will not be used, as no baseline characteristics are expected to significantly influence the study outcomes. Blinding of the treatment allocation after randomisation is not feasible, as both patients and care providers will be aware of the hospital setting in which the follow-up takes place.

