## Introduction

Globally, head and neck cancer (HNC) is the 7th most common cancer diagnosis [1]. The most common primary sites include carcinomas of the oral cavity, pharynx and larynx. In recent years, the overall incidence of HNC in the Netherlands has increased, mainly due to the rise in human papilloma virus-related squamous cell carcinoma of the oropharynx [2, 3].

Aiming to detect cancer without delay and identify recurrences early, patients follow a rigorous post-treatment schedule. In the Netherlands, follow-up for HNC patients is centralised in head and neck oncology centres (HNOCs) [4]. Dutch guidelines advise visits every 2 to 3 months during the first 2 years, and every 4 to 6 months in the following 3 years [4]. This applies to all HNC patients, despite significant differences in recurrence rates and prognosis [2]. Centralised care requires some patients to travel long distances, creating financial and practical burdens for them and their caregivers [5, 6]. With a growing patient population, head and neck oncologists also face challenges in maintaining oncologic (follow-up) care. There are several efforts to address rising costs and burden, advocating for digital innovations, regional cooperation and sustainable solutions [7].

The need to revise the patient-care pathway is also internationally recognised and extends beyond HNC to other oncological fields [8–12]. One proposed solution is patient-initiated follow-up, where patients schedule consultations based on symptoms, abandoning a generalised schedule [8, 13]. However, this may be less sustainable for older or frail patients. Evidence that routine follow-up for (head and neck) cancer improves clinical outcomes is generally lacking [14, 15]. An exception may be early-stage glottic carcinoma after transoral laser surgery (TOLS), for which reported recurrence rates vary widely, ranging from 9 to 25% depending on the tumour stage and follow-up duration [16–19]. Early detection may allow limited revision surgery instead of escalating to multimodality treatment with radiotherapy [14, 15, 17, 20]. Patients also report that follow-up reduces fear of recurrence and provides psychosocial support [12]. Follow-up for HNC usually includes high definition (HD)-laryngoscopy, which has a high detection rate for malignancies, and adding narrow-band-imaging (NBI) improves detection even further [16, 21].

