### Eligibility criteria

Inclusion criteria include patients who underwent TOLS for severe dysplasia, carcinoma-in-situ or T1 squamous cell carcinoma, have a one-way travel time (by car) to the HNOC of > 45 min and have the possibility of follow-up in a nearby participating hospital. In addition, patients are eligible for inclusion if they are within 2 years postoperatively and can speak and write Dutch (Figure 1). Patients will be excluded if they continue to undergo follow-up for other cancers in the HNOC. Written informed consent will be obtained from all patients (Supplementary information B).

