### Interventions

Figure 1 visualises the study flow. Included patients will be randomly assigned to one of two groups: an intervention group and a control group. Follow-up is performed though standardised follow-up guidelines and is equal for all patients, with at least of 4 to 6 consultations expected [4]. The control group will receive their oncological follow-up in the UMCG. The intervention group will receive their oncological follow-up by an ENT surgeon in a hospital that is closer to the patients’ home. A reduction in travel time of more than one-third was considered indicative of closer proximity to home, as it is believed that it would be a significant time reduction for the patients. A history will be taken, and a complete ENT physical examination will be performed, including flexible HD-video laryngopharyngoscopy (with or without NBI) and neck palpation. HD-laryngopharyngoscopy is performed with digital transnasal flexible endoscopes of XION (XION GmbH, Berlin, Germany) or Olympus (Olympus Nederland BV). The videos obtained during the follow-up visit will be digitally transferred and securely stored in the electronic patient files in the HNOC, for the same day assessment by a head and neck oncologist. Furthermore, the head and neck oncologist has access to the patients’ previous examinations, (surgical) history and findings or concerns of the ENT surgeon who has seen the patient earlier that day. After evaluation, the patient is contacted by the HNOC to share the results, and a new management plan (such as re-referral to the HNOC) is formulated if necessary.

Patients who do not wish to participate in this randomised controlled study will be asked to complete the questionnaires that are part of this study whilst receiving their follow-up in HNOC (the ‘preference group’).

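### The reason given for not stratifying conflicts with the protocol's own account of recurrence and visit schedule; delete it and adjust the affected secondary comparisons

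*Protocol article*

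**What the plan says.** Protocol article, Allocation to study groups: "Randomisation will be performed in REDCap with a 1:1 allocation ratio", followed by "Block randomisation and stratification will not be used, as no baseline characteristics are expected to significantly influence the study outcomes". The reason refers to the study outcomes as a whole, not to the primary outcome alone.

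Introduction, on early glottic carcinoma after laser surgery: "reported recurrence rates vary widely, ranging from 9 to 25% depending on the tumour stage and follow-up duration". The same section gives the Dutch guideline schedule as "visits every 2 to 3 months during the first 2 years, and every 4 to 6 months in the following 3 years".

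Eligibility criteria: the trial takes "patients who underwent TOLS for severe dysplasia, carcinoma-in-situ or T1 squamous cell carcinoma", and "patients are eligible for inclusion if they are within 2 years postoperatively". Lesion type and time since surgery therefore both differ between patients at entry.

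Outcomes and Table 1: recurrence is a safety outcome. Visit frequency, total travel distance and CO2 emission are listed under other outcomes.

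Interventions: follow-up is described as the same for everyone, "with at least of 4 to 6 consultations expected".

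Statistical analysis: the between-group tests named are the t-test, rank tests and chi-squared, all unadjusted.

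**The concern.** One sentence carries the whole justification for the allocation method, and the Introduction contradicts it. If stage influences recurrence, and time since treatment sets how often a patient attends, then at least two baseline characteristics influence listed outcomes.

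The reason also has no bearing on blocking. Blocks control arm sizes, whatever the covariates do, so an absence of prognostic factors would not be an argument against them.

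What is at stake is the reading of the secondary comparisons. The trial wants to say whether the two forms of follow-up are equally safe, and recurrences will be few. A chance difference between arms in lesion type or time since surgery would be hard to separate from an effect of the follow-up location if only unadjusted tests are reported.

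**Working it through.** **1. Statements side by side**

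| Factor at entry | What the Introduction ties to it | Listed outcome affected |
|---|---|---|
| Lesion type (three admitted) | Recurrence, 9 to 25% by stage and follow-up duration | Recurrence (safety) |
| Time since surgery (0 to 24 months) | Visit interval: 2–3 months, then 4–6 months after year 2 | Visit count, travel distance, CO2 |
| Either | Nothing stated | Satisfaction (primary) |

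CO2 is computed as distance times 130.1 g per km, so any shift in distance carries over proportionally.

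**2. Visits implied by the schedule**

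Visits = (months before month 24)/(interval of 2–3) + (months after month 24)/(interval of 4–6). This assumes that the guideline's clock starts at surgery. Over 12 months on study:

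- Entry at month 0 to 12: 12/3 = 4 to 12/2 = 6. This reproduces the stated 4 to 6.
- Entry at month 18: 6/3 + 6/6 = 3 to 6/2 + 6/4 = 4.5.
- Entry at month 24: 12/6 = 2 to 12/4 = 3.

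Over 24 months on study, entry at month 24 gives 24/6 = 4 to 24/4 = 6. The stated minimum therefore fails for late entrants over 12 months and holds over 24 months.

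**3. Chance imbalance in a binary factor**

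With 45 per arm and 50% prevalence (assumption), the SD of the between-arm difference is √(2 × 0.25/45) = 0.105. Simulating simple randomisation of 90 patients (200,000 draws), with prevalence of 30 to 50% assumed:

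- gap of at least 15 points: 13 to 17%;
- gap of at least 20 points: 4 to 7%.

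**4. What a 20-point gap would do**

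- Recurrence: if the ends of the quoted range were the rates of the two lesion groups (assumption; the document gives no rate per lesion), the shift is 0.20 × (0.25 − 0.09) = 0.032, or 0.032 × 45 ≈ 1.4 events. At 17% recurrence, the midpoint of 9 and 25%, the standard error of the difference is √(2 × 0.17 × 0.83/45) ≈ 0.079.
- Visits: in the extreme contrast of entry at month 24 against entry by month 12, the shift over 12 months is 0.20 × (4 − 2) = 0.4 to 0.20 × (6 − 3) = 0.6 visits. Real contrasts would be smaller.

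**5. Arm sizes**

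The chance of a 40:50 split or worse is 2 × P(Bin(90, 0.5) ≤ 40) = 0.343. Power of a two-sided 5% t-test (difference 1, SD 1.8, no dropout):

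- 45:45 gives 74.1%;
- 40:50 gives 73.6%;
- 37:53 (11% chance of this or worse) gives 72.7%.

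The standard error at 40:50 rises by the factor √[(1/40 + 1/50)/(2/45)] = 1.006.

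Power is below the planned 80% even with equal arms, because the stated 41 per group matches a one-sided calculation. That is a separate matter and does not change the comparison between splits.

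**The case against.** The case for leaving the allocation alone is strong in several respects.

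- **Primary outcome.** A reader might infer that the main comparison is compromised. The document does not support that: it links neither lesion type nor time since surgery to satisfaction, and the sample size rests on satisfaction alone. This stands.
- **Precision.** The 34% chance of a 40:50 split or worse looks alarming, since it leaves one arm below 41 before dropout. At 40:50 it costs about half a power point. This stands.
- **Recurrence contrast.** It is tempting to read 25% as the T1 rate and 9% as the rate for the other lesions. The range covers reported studies of early glottic carcinoma and is attributed to stage and follow-up duration together. Follow-up duration there describes those studies and is not evidence that time since surgery at entry predicts recurrence. Applying the range here (0.09 × 45 ≈ 4 to 0.25 × 45 ≈ 11 recurrences per arm) is also an assumption, because the trial includes dysplasia.
- **Validity.** Simple randomisation is unbiased, and chance imbalance is already part of the sampling error. Unblocked allocation is also the least predictable choice in an open trial. Both points stand, although the protocol does not give predictability as its reason.
- **Consultations.** One might call the expected 4 to 6 plainly wrong. The Interventions section names no period, and the Outcomes section speaks of at least 1 year for secondary outcomes and aims at 2 years for safety. The conflict arises only over 12 months, and the follow-up figure is not shown.
- **Analysis plan.** Covariate adjustment may be specified in a document not shown here.

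None of this rescues the sentence itself, which speaks of the study outcomes without restriction.

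**Conclusion.** The stated reason for not stratifying is contradicted by the Introduction, for recurrence through tumour stage and for visit count, travel distance and CO2 through time since treatment. The contradiction is confined to secondary and other outcomes. It does not invalidate the randomisation or weaken the primary comparison to any useful degree.

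The practical size is modest. A 20-point imbalance in lesion type is a 4 to 7% event at an assumed prevalence of 30 to 50%. It would move recurrence by about 3.2 points under an assumed 25% against 9% contrast, less than half of the roughly 7.9-point standard error. The case for acting is that the correction is nearly free and the safety comparison has few events. The number of expected consultations is an ambiguity to be reconciled, not a demonstrated error.

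**What to change.** 1. Delete the claim that baseline characteristics do not matter. If unblocked allocation is preferred because it is hard to predict in an open trial, say so.
2. Keep the allocation list. Compare recurrence stratified by or adjusted for lesion type (dysplasia or carcinoma in situ against T1). Compare visit count, travel distance and CO2 adjusted for time since surgery. Show the unadjusted results as well. Both variables can be drawn from the tumour data and surgical history already collected at baseline.
3. State the period to which the expected 4 to 6 consultations apply, and reconcile that number with the guideline schedule for patients entering late in the 2-year window.
4. If randomisation has not begun, stratifying by lesion type with concealed, randomly varying block sizes is an option, not a necessity.

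The cost is a little more analysis, and sparse strata if recurrences are few. Option 4 would need a new allocation table from the independent researcher and would make allocation slightly more predictable.
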